## Abstract

**Background:**

Stroke survivors have long-term upper limb impairment, which impacts the quality of life (QOL) and social reintegration, but there is lack of effective therapeutic strategies and novel technologies. Customized multi-muscle functional electrical stimulation (FES) based on the muscle synergy of healthy adults and robotic-assisted therapy (RAT) have been proved efficacy respectively. Synergy-based FES combined with RAT can be a novel and more effective therapy for upper limb recovery of stroke survivors from the perspective of synergistic enhancement. However, few studies have examined the effectiveness of combined synergy-based FES and RAT, especially for motor control evaluated by reach-to-grasp (RTG) movements. The main objective of the following research protocol is to evaluate the effectiveness and efficacy, as well as adoptability, of FES-RAT and FES or RAT rehabilitation program for upper limb function improvement after stroke.

**Methods:**

This will be an assessor-blinded randomized controlled trial involving a 12-week intervention and a 6-month follow-up. Stratified randomization will be used to equally and randomly assign 162 stroke patients into the FES + conventional rehabilitation program (CRP) group, RAT + CRP group and FES-RAT + CRP group. Interventions will be provided in 5 sessions per week, with a total of 60 sessions. The primary outcome measurements will include the Fugl-Meyer Assessment and Biomechanical Assessment of RTG movements. The secondary outcome measurements will include quality of life and brain neuroplasticity assessments by MRI. Evaluations will be performed at five time points, including at baseline, 6 weeks and 12 weeks from the start of treatment, and 3 months and 6 months following the end of treatment. A two-way analysis of variance with repeated measures will be applied to examine the main effects of the group, the time factor and group-time interaction effects.

**Discussion:**

The results of the study protocol will provide high quality evidence for integrated synergy-based FES and RAT, and synergy-based FES alone and guide the design of more effective treatment methods for stroke rehabilitation.

**Trial registration:**

ChiCTR2300071588.

**Supplementary Information:**

The online version contains supplementary material available at 10.1186/s12883-023-03369-2.

## Background

Stroke is the leading cause of long-term disability among middle-aged and elderly adults worldwide [1, 2]. Approximately 70–80% of stroke survivors have limb motor impairments, especially upper limb impairment, which directly impacts the quality of life (QOL) and social reintegration [3]. There is an important effort worldwide to establish therapeutic strategies and novel technologies to improve upper limb function after stroke, such as functional electrical stimulation (FES) [4], robotic-assisted therapy (RAT) [5], and task-oriented therapy (TOT) [6]. Unfortunately, six months after stroke, approximately 65% of patients still cannot incorporate the affected arm and hand into their daily activities [7, 8]. Therefore, the primary goal in the clinical field of upper limb rehabilitation for stroke patients is the continuous exploration of novel and effective treatment therapies.

The central nervous system (CNS) recruits a reduced and fixed set of coordinated patterns of muscle activities to generate a vast variety of movements, which is defined as muscle synergy [9, 10], and several neuroscience studies have demonstrated that muscle synergy is the neurological mechanism of motor execution and control [11, 12]. Compared with healthy controls or the unaffected side, the affected side of stroke patients showed reduced synergy and merged motor modules, which is closely related to poor motor function and motor control [13, 14]. It is likely that this reduction is caused by a lack of independence of the corticospinal drive to the spinal cord, which ultimately results in poor muscle control [15, 16]. Thus, muscle synergy could be a potential ground upon which novel therapies aimed at enhancing motor relearning could be designed, especially for multi-muscle FES therapy.

In this scope, FES training based on muscle synergies in healthy individuals has been recently proposed for the forward-reaching upper limb movements of stroke patients [12, 17, 18]. Specifically, synergy-based FES had instantaneous effects on upper limb motor functions poststroke after 1 session of training, and the potential benefits included increased velocity and motor functionality [11]. The research team of Niu from Ruijin Hospital further verified the short-term (five-day training) efficacy of synergy-based FES for upper limb function based on small samples (9 participants with stroke) [17]. These results demonstrated that synergy-based FES has potential value for improving upper limb motor performance and function. However, the lack of randomized controlled trials with larger sample sizes and evidence of the long-term efficacy of synergy-based FES for upper limb function improvement after stroke might affect its clinical application.

Unlike synergy-based FES, which activates weak muscles, robotic-assisted therapy (RAT) is another upper limb rehabilitation approach that allows for intensive, high-frequency repeat training in accordance with the principles of motor learning [6, 19–21]. More importantly, thus far, the RAT training system could design an accurate movement trajectory that fits activities of daily living (ADLs) as a training target for driving optimal control strategies in real environments, such as reach-to-grasp (RTG) movements. Previous systematic reviews have reported that RAT for the affected upper limb can improve arm-hand performance and health-related quality of life in stroke survivors [6]. Both rehabilitation approaches act on different aspects of motor learning: by means of FES, activation of the neuromotor trajectories is reinforced by exploiting the intentional will of a subject to activate their muscles within a specific task, while through robotic therapy, it is possible to perform a large number of repetitions [21].

Perhaps the best stroke rehabilitation program should combine rehabilitation therapies with definite efficacy on motor function that act on different aspects of motor relearning principles to maximize motor function improvement in stroke survivors [21–23]. It has been proposed that when muscles are activated by electric stimulation and other forms of physical exercise (i.e., RAT, task-oriented training) make voluntary efforts or provide the major interaction effect, a synergistic-enhanced rehabilitation effect may be produced [7, 21]. From this perspective, synergy-based FES combined with RAT may be a novel and more effective therapy for upper limb function enhancement in stroke survivors. However, to our knowledge, few studies have examined the effectiveness and safety of combined synergy-based FES and RAT for upper limb function improvement in stroke patients, especially for motor control in RTG movements. Therefore, the present protocol was designed for an assessor-blinded randomized controlled trial, which will include 3 groups: the FES + CRP group, RAT + CRP group and FES-RAT + CRP group. The purposes of this protocol are as follows:

### Aim 1

To provide high-quality evidence of synergy-based FES for improvement of the upper limb function after stroke.

### Aim 2

To examine the effectiveness and safety of combined synergy-based FES and RAT for upper limb function improvement after stroke.

### Aim 3

To compare the efficacy differences in upper limb function improvement after stroke between the FES-RAT therapy and FES or RAT groups.

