## Methods

### Study design

This will be a single-center, assessor-blinded randomized controlled trial (RCT) involving a 12-week intervention and 6-month follow-up. A total of 162 patients with stroke will be recruited and randomly assigned to the FES + CRP group, RAT + CRP group and FES-RAT + CRP group at a ratio of 1:1:1. Figure 1 depicts a concise flowchart of the entire study, and Table 1 provides the schedule of events. The study protocol (2023-7th-HIRB-034) was approved by the Ethics Committee of the Seventh People's Hospital of Shanghai University of Traditional Chinese Medicine and registered in the Chinese Clinical Trial Registry (ChiCTR2300071588).

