### Participants

#### Inclusion criteria

The following criteria must be met for inclusion: (1) patients aged between 19 and 80 years old; (2) patients with first-ever stroke, with a time since stroke onset ≤ 3 months; (3) patients with unilateral right or left-sided stroke; (4) patients with a Mini-Mental State Examination score > 24 [26]; (5) patients with at least minimal antigravity movement in the affected upper limb; (6) patients with at least 5 degrees of wrist extension in the antigravity position; (7) patients without hemi-spatial neglect; and (8) patients who sign the informed consent form.

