### Intervention

The rehabilitation intervention will be administered at the rehabilitation medical center of the Seventh People’s Hospital of Shanghai University of Traditional Chinese Medicine. All participants will receive the CRP recommended by the neuro-rehabilitation guidelines [28, 29], which will include stretching, passive and active limb movements, proprioceptive neuromuscular facilitation, muscle strengthening, and different reaching, grasping and manipulating actions that are motivational and appropriate for the participants. Based on the CRP (20 min), Group A will receive FES (20 min); Group B will receive RAT (20 min); and Group C will receive FES-RAT (20 min). The intervention for the three groups will be provided for 60 sessions (5 sessions per week, 12 weeks), each lasting 40 min.

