We recognize that this study also has limitations. This research has an inevitable limitation associated with the difficulty in controlling the methodology of blinding during the RAT intervention because the participants and therapists cannot be blinded due to the visibility of the RAT intervention. Although the outcome assessors and data analyzer will be blinded to the group allocation, there might still be a risk of detection bias during the study’s implementation. Additionally, muscle synergy extraction, FES and RAT training in this study need to be performed by medical personnel in medical institutions, which may limit the promotion and application of synergy-based FES and RAT in the community and home settings. Furthermore, based on the results of a few recent studies, there were no differences between intracerebral hemorrhage and cerebral infarction of function prognosis at rehabilitation discharge, so when including patients, we didn’t make a clear distinction on whether different types of strokes will affect the intervention outcomes, which should be investigated in further study.

In summary, the results of the study protocol will achieve multiple study purposes, including demonstrating the effectiveness of synergy-based FES, and synergy-based FES-RAT for improving upper limb function after stroke and exploring the efficacy differences in improving upper limb function after stroke between the FES-RAT therapy and FES or RAT. Synergy-based FES combined with RAT may have a potential opportunity to better improve the upper limb function of stroke survivors. These results of the study will provide high-quality evidence for integrated synergy-based FES and RAT and synergy-based FES alone and guide the design of more effective treatment methods for stroke rehabilitation.

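### With conventional rehabilitation plus an active device in every arm, the trial cannot show what synergy-based FES adds to conventional rehabilitation, yet its planned conclusions say it will

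*Protocol article*

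**What the plan says.** Study design has 162 patients "randomly assigned to the FES + CRP group, RAT + CRP group and FES-RAT + CRP group at a ratio of 1:1:1". Under Intervention, "All participants will receive the CRP recommended by the neuro-rehabilitation guidelines": 20 minutes of CRP in each session, followed by 20 minutes of FES, RAT or FES-RAT according to arm. The text describes no CRP-only or sham arm. Figure 1 and Table 1 are not shown, but the wording on arms is unambiguous.

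The Background lists three aims. Aim 1 is "To provide high-quality evidence of synergy-based FES for improvement of the upper limb function after stroke". Aim 2 concerns the effectiveness and safety of the combination. Aim 3, listed separately, is "To compare the efficacy differences in upper limb function improvement after stroke between the FES-RAT therapy and FES or RAT groups".

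The last paragraph of the Discussion says the trial will achieve several purposes, "including demonstrating the effectiveness of synergy-based FES, and synergy-based FES-RAT for improving upper limb function after stroke". That paragraph and the Discussion part of the Abstract also promise high-quality evidence for synergy-based FES by itself as well as for the combination.

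The Inclusion criteria admit "patients with first-ever stroke, with a time since stroke onset" of at most 3 months. Statistical analysis plans tests of group, time and their interaction, with simple effects when the interaction is significant.

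**The concern.** A claim that FES is effective needs a comparator without FES that is otherwise the same. For FES given with conventional rehabilitation, that comparator is conventional rehabilitation, and no arm receives it alone. The result that looks closest to answering Aim 1 is improvement over time in the FES + CRP arm. In these patients, improvement would be expected from recovery and from 60 sessions containing CRP even if FES did nothing. That is a clinical expectation; the article gives no figure for it.

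What is at stake is the conclusion. If the arms improve together and do not differ, the planned wording would claim effectiveness of FES with no randomised support. The limitations paragraphs of the Discussion cover blinding, setting and stroke type, but not the comparator.

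**Working it through.** **Inputs.** Arms and background treatment come from Study design and Intervention, and the enrolment window from Inclusion criteria. From Sample size calculation: a RAT versus CRP difference of 4.50 points on the FMA-UE, a reference difference of 4.25, SD 6, 129 evaluable patients, 20% dropout, 162 in total.

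**Step 1: what each arm's mean change contains.** Let *c* be the mean change under CRP alone, recovery included. Let *F* and *R* be the effects of adding FES or RAT to CRP, and *I* any extra effect, positive or negative, of giving both together.

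- FES + CRP: *c + F*
- RAT + CRP: *c + R*
- FES-RAT + CRP: *c + F + R + I*

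**Step 2: the randomised contrasts.**

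| Contrast | Estimates | Bearing on FES |
|---|---|---|
| FES-RAT minus RAT | *F + I* | FES as an add-on to RAT |
| FES minus RAT | *F − R* | FES against another active treatment |
| FES-RAT minus FES | *R + I* | RAT as an add-on to FES |

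The third contrast is the first minus the second, so there are two independent contrasts for three unknown effects. *F* is not among the estimable quantities.

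**Step 3: *F* cannot be recovered indirectly.** Replace (*c, F, R, I*) by (*c + d, F − d, R − d, I + d*). All three arm means stay the same for any *d*. As an illustration, apply the planning difference of 4.50 to both devices (an assumption for FES):

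- Scenario A, *F = R* = 4.50 and *I* = 0: arm means *c* + 4.50, *c* + 4.50 and *c* + 9.00.
- Scenario B, *F = R* = 0, *I* = 4.50, and CRP with recovery larger by 4.50: arm means (*c* + 4.50) + 0, (*c* + 4.50) + 0 and (*c* + 4.50) + 4.50 = *c* + 9.00.

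The trial would see the same data in both, with FES-RAT minus RAT equal to 4.50. In A, FES is worth 4.50 points over CRP. In B it is worth nothing unless given with RAT. Setting *I* = 0 would identify *F*, but the Background's rationale is that the two therapies reinforce each other, which means *I* > 0.

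**Step 4: change over time.** Within-arm change in FES + CRP is *c + F*, and the time main effect averages all three arm means. Neither separates *F* from *c*.

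**Step 5: sample size is not the obstacle.** The dropout step reproduces: 129/0.8 = 161.25, rounded up to 162 = 3 × 54. The 129 itself did not reproduce from the stated inputs (235, or 237 with equal arms, for the between-group effect; 63 for the interaction). That is a separate question, and nothing here rests on it. With 129/3 = 43 evaluable per arm, the standard error of a pairwise difference is 6 × √(2/43) = 1.294, and 4.25/1.294 = 3.284. By the normal approximation, power is Φ(3.284 − 1.960) = 0.91 at two-sided alpha 0.05 and Φ(3.284 − 2.394) = 0.81 at 0.05/3. Contrasts of the planned size are within reach, but more patients in the same three arms would still not supply *F*. The effect used for planning, RAT versus CRP, is likewise a contrast this trial does not contain.

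**The case against.** The strongest case for the plan is that Aim 1 does not name CRP as the comparator, and that the trial does randomise FES. FES-RAT versus RAT differs by design only in FES: both arms have the same CRP and session length, and the FES-RAT section keeps frequency, repetitions and rest consistent with the separate treatments. If that contrast is positive, FES works as an add-on to RAT. If FES + CRP beats RAT + CRP, FES is superior to a treatment the Background describes as beneficial. It would then also be better than CRP, provided RAT is no worse than CRP, which this trial does not test.

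All of this stands, and it rules out several stronger readings that a reader might infer:

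- That the trial holds no randomised evidence on FES, or that no result could support a claim about it. Two of the three contrasts bear on FES.
- That Aim 2 cannot be answered. It does not name CRP either, and the combination is compared with each single modality.
- That a non-inferiority margin or a conventional-FES arm is missing. The article neither argues effectiveness from similarity to RAT nor claims that the synergy-derived pattern is better than other FES.
- That the authors intend to treat the time effect as proof. Statistical analysis lists it as one of the tests and says nothing about how it will be interpreted.

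The objection does not rescue the wording on FES by itself. An add-on effect on top of RAT is a different quantity, and Aim 3 already covers the comparisons between devices.

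**Conclusion.** The point holds as a mismatch between the arms and the stated conclusions. None of the three pairwise contrasts estimates FES + CRP against CRP, and no enlargement of the existing arms would change that. The unqualified statement that FES will be shown effective, and the promise of evidence for FES by itself, therefore go beyond the design. The trial can support narrower statements: FES added to RAT, FES against RAT, and the combination against each component. Aim 3 is unaffected.

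The conclusion rests on the arms as described in the text. It needs no figure for natural recovery, because the confounding of *F* with *c* is structural. It does not imply that the trial is too small or that its analysis of the between-arm contrasts is invalid.

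**What to change.** Change wording only; no arm needs to be added.

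1. Restate Aim 1 as estimating (a) the effect of adding synergy-based FES to RAT + CRP, from FES-RAT versus RAT, and (b) the difference between FES + CRP and RAT + CRP.
2. Restate the effectiveness part of Aim 2 as FES-RAT versus FES and FES-RAT versus RAT.
3. Add to Statistical analysis that the time main effect and within-arm change will be reported descriptively and will not be interpreted as treatment effectiveness.
4. In the Abstract and Discussion, remove or qualify the statements about demonstrating the effectiveness of FES and providing evidence for FES by itself, and list the absence of a CRP-only comparator among the limitations.

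This rewording does not require choosing a time point; that is a separate decision.

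The cost is narrower claims and a wording update to the protocol and registry. Recruitment began on 1 May 2023. Allocation, treatment, assessments and sample size all stay as they are.

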## Methods

### Study design

This will be a single-center, assessor-blinded randomized controlled trial (RCT) involving a 12-week intervention and 6-month follow-up. A total of 162 patients with stroke will be recruited and randomly assigned to the FES + CRP group, RAT + CRP group and FES-RAT + CRP group at a ratio of 1:1:1. Figure 1 depicts a concise flowchart of the entire study, and Table 1 provides the schedule of events. The study protocol (2023-7th-HIRB-034) was approved by the Ethics Committee of the Seventh People's Hospital of Shanghai University of Traditional Chinese Medicine and registered in the Chinese Clinical Trial Registry (ChiCTR2300071588).

**Fig. 1 Fig1:**
[figure not shown]
A brief flowchart of the entire study. Note: FES, Functional Electrical Stimulation; CRP, Conventional Rehabilitation Program; RAT, Robotic-Assisted Therapy; FMA, Fugl-Meyer Assessment; RTG, Reach-To-Grasp; QOL, Quality of Life

**Table 1 Tab1:**
[figure not shown]
Schedule of enrollment, intervention and assessments

“✓” means the item will be completed. *FES *Functional electrical stimulation, *CRP *Conventional rehabilitation programs, *RAT *Robotic-assisted therapy, *FMA *Fugl-Meyer Assessment, *RTG *Reach-To-Grasp, *BI *Modified Barthel Index, *SS-QOL *Stroke-Specific Quality of Life Scale

### Sample size calculation

The G*power software was utilized to determine the minimum sample size required to detect a significant between-group difference in the present research [24]. In a study of RAT for upper-extremity poststroke rehabilitation, Takebayashi et al. [25] used the minimal clinically significant difference as a reference (4.25 points), the mean difference in the FMA-UE score between patients in the RAT and CRP was 4.50 points and standard deviations between patients were 6. Based on a prior two-way repeated analysis of variance (ANOVA) F test, with a power of 0.80, an effect size of 0.158, three groups, five measurements, correlation among repeated measures of 0.5, and an alpha level of 0.05, 129 participants were required for this study. To account for a conservative drop-out rate of 20%, the final sample size will therefore be 54 participants in each group, for a total of 162 participants.

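### The printed inputs give 235 participants for the between-group test, not 129, and the effect size of 0.158 is not derived from the cited 4.50 points, so the 80% power claim is unsupported as written

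*Protocol article*

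**What the plan says.** The Sample size calculation section of the protocol article states its purpose as to "determine the minimum sample size required to detect a significant between-group difference in the present research". It cites an earlier trial of robotic therapy in which "the mean difference in the FMA-UE score between patients in the RAT and CRP was 4.50 points". The SD it takes from that trial is 6, and it gives 4.25 points as the minimal clinically significant difference.

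The method is described as "Based on a prior two-way repeated analysis of variance (ANOVA) F test". Its main inputs are quoted as "with a power of 0.80, an effect size of 0.158, three groups, five measurements"; the assumed correlation between visits is 0.5. The result reads "an alpha level of 0.05, 129 participants were required for this study", raised to 54 per arm (162 in all) for 20% dropout.

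The section does not say which F test is powered (group, time or group-by-time), gives no nonsphericity epsilon, and does not show how 0.158 was obtained. The Statistical analysis section plans all three effects, with Bonferroni correction for multiple comparisons.

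**The concern.** The article prints what looks like a full set of inputs and one answer, so the answer can be checked, and for the stated purpose it does not come out. There are two separate breaks in the chain: from the cited 4.50 points and SD 6 to f = 0.158, and from f = 0.158 to 129.

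At stake is what the 80% refers to. As printed, it cannot be tied to a particular effect or to a difference in FMA-UE points. A reader of the results could not say what difference between arms the trial was sized to detect, and the effect size implied by 0.158 is about half the minimal difference cited in the same paragraph.

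**Working it through.** **Inputs (Sample size calculation):** f = 0.158, k = 3 groups, m = 5 measurements, ρ = 0.5, α = 0.05, power 0.80; reference difference 4.50, SD 6, minimal difference 4.25. Epsilon (ε) is not stated; ε = 1 means sphericity.

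**1. Can 129 be reproduced?** Noncentral F, with the software's default repeated-measures formulas:

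- Group effect: λ = N f² m / [1 + (m − 1)ρ], df = k − 1 and N − k. Here f² = 0.024964 and m / [1 + (m − 1)ρ] = 5/3, so λ = 0.0416 N. Power first reaches 0.80 at N = 235 (λ = 9.78); equal arms need 237. Epsilon does not enter this test.
- Interaction: λ = N f² m ε / (1 − ρ), df = (k − 1)(m − 1)ε and (N − k)(m − 1)ε. At ε = 1, λ = 0.2496 N and N = 63.
- Time effect: same λ, df = (m − 1)ε and (N − k)(m − 1)ε. At ε = 1, N = 50 (51 in equal arms).

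| Effect at f = 0.158, ε = 1 | N for 80% power | Power at 129 | Power at 162 |
|---|---|---|---|
| Group | 235 (237 in equal arms) | 0.524 | 0.629 |
| Group-by-time | 63 | 0.993 | 0.999 |
| Time | 50 (51 in equal arms) | 0.998 | >0.999 |

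Settings that do give 129 in equal arms: the time effect at the lower bound ε = 1/(m − 1) = 0.25 (power 0.804), and the interaction at ε of about 0.34. Neither is stated. The software's alternative effect-size conventions at ε = 1 give 121 to 124 for time and 153 to 156 for the interaction before rounding to equal arms.

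**2. Does 0.158 follow from 4.50 and SD 6?** d = 4.50/6 = 0.75.

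- Two groups: f = d/2 = 0.375.
- Three groups, evenly spread means: f = d/√6 = 0.306.
- Three groups, one arm differing: f = d√2/3 = 0.3536.

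For 4.25 points the range is 0.289 to 0.354. None is 0.158. In reverse, f = 0.158 at SD 6 is 2 × 0.158 × 6 = 1.90 points (two-group conversion), 0.158 × 6 × 3/√2 = 2.01 (one arm differing) or 0.158 × 6 × √6 = 2.32 (evenly spread).

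One match exists: 0.3536/√5 = 0.1581, the one-arm-differing f divided by the root of the number of visits. The text shows no such step, and it is not the usual f for a group effect.

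**3. Power if the cited difference is taken at face value.** Group effect, N = 129: 0.984 at f = 0.306, 0.998 at f = 0.3536, 0.999 at f = 0.375.

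**4. What 129 evaluable participants can detect.** Solving the group-effect formula for 80% power gives f = 0.214. At SD 6 and ρ = 0.5 the largest difference between arms is 0.214 × 6 × 3/√2 ≈ 2.73 points (one arm differing) to 0.214 × 6 × √6 ≈ 3.15 points (evenly spread), held across visits.

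For a pairwise comparison at a single visit (an assumption), 43 per arm, two-sided α = 0.05/3 and noncentral t give d = 0.710, and 0.710 × 6 = 4.26 points. Power is 0.798 at 4.25 points and 0.847 at 4.50.

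**5. Dropout step.** 129/0.8 = 161.25, rounded up to 162 = 3 × 54. This is correct.

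**The case against.** The best case for the protocol is that 129 and 0.158 each have a possible origin. The time effect with lower-bound epsilon returns exactly 129, and 0.158 equals 0.3536/√5 to three decimals. A condensed article may leave the epsilon and the chosen effect to a fuller document. This stands to the extent that 129 cannot be called unreachable, nor 0.158 unrelated to its source. It does not repair the claim. The time effect asks whether patients change on average over the visits, not whether arms differ, and for the group effect no epsilon setting matters.

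A reader might go further and infer that the trial is underpowered, because the group test has power 0.52 at 129. The document does not support that. The 0.52 holds only at f = 0.158, a value whose basis is not shown; at the cited 4.50 points and SD 6 the same test exceeds 98%. Nor would a null result be uninterpretable: the Statistical analysis section promises 95% confidence intervals, which can be read against the printed 4.25 points.

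It can also be said that the cited difference is openly labelled as a reference from another study. That is fair. But it compares RAT with CRP, and under Intervention every arm here receives CRP plus an active add-on, so no arm is CRP alone and nothing shown makes 4.50 points the expected difference between these arms.

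**Conclusion.** The point holds in this form. For the between-group purpose the section states, the printed inputs require 235 participants (237 in equal arms), not 129. At ε = 1 neither of the other two effects gives 129 under the default formulas. The value 0.158 is not the usual f for 4.50 points with SD 6, and its derivation is not shown. The claim of 80% power is therefore unsupported as written, while the adequacy of 162 is not disproved.

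These results assume the noncentral F formulas above, equal arms, a common SD of 6 and a correlation of 0.5 between every pair of visits. The figures in points also depend on the pattern of the three means, which is why they are given as ranges.

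**What to change.** Keep 162. In the Sample size calculation:

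- Remove f = 0.158 and the statement that it yields 129.
- Name the effect being powered, group or group-by-time, and give the epsilon if it is the interaction.
- State the detectable difference for that test. For the group effect with 129 evaluable, this is f of about 0.21 with 80% power, a largest difference between arms of about 2.7 to 3.15 points at SD 6 and ρ = 0.5.
- If Bonferroni pairwise comparisons at one visit are the intended test, say so and name the visit, since the article names none. With 43 per arm and α = 0.05/3 the detectable difference is then about 4.26 points, close to the cited 4.25.
- Say that the 4.50-point reference is RAT versus CRP, a contrast this trial does not contain.

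The cost is one rewritten paragraph and no extra patients. The sponsor has to commit to one powered effect and accept whatever detectable difference goes with it.

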### Statistical analysis

All statistical analyses will be performed with IBM SPSS (IBM Corp. Released 2013. IBM SPSS Statistics for Windows, Version 22.0. Armonk, NY: IBM Corp.) by statisticians who are blinded to the group allocation. The analyses will be performed on an intention-to-treat basis. The Shapiro–Wilk (SW) test will be used to examine the normal distribution of the continuous variables comprising demographic and outcome measures. Continuous variables will be described as the mean ± SD for those with normal distributions or the median for those with nonnormal distributions, and categorical variables will be described as the frequency. The χ^2^ test or Fisher’s exact test will be used to examine the comparisons among the three groups for categorical variables. When the normality of data distribution is determined, two-way of variance with repeated measures will be applied to examine the main effects of the group and time factors, as well as the group-time interaction effects. A simple effect post hoc analysis will be conducted when the time-group interaction is significant. Furthermore, the linear mixed model will be adjusted for age, sex and type of stroke if homogeneity is not found. The significance level for all statistical tests will be set at 0.05, corrected for multiple comparisons using the Bonferroni-adjusted method and accompanied by a 95% confidence interval.

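### The printed G*Power inputs do not return 129 for any effect of the two-way repeated-measures ANOVA, and the effect being powered is not named

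*Protocol article*

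**What the plan says.** All of the calculation is in the Sample size calculation section of the protocol article.

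- **Purpose.** G*Power was used to "determine the minimum sample size required to detect a significant between-group difference in the present research".
- **Test.** "Based on a prior two-way repeated analysis of variance (ANOVA) F test". The sentence does not say whether the group, time or interaction effect was sized.
- **Inputs and result.** "with a power of 0.80", then "an effect size of 0.158, three groups, five measurements, correlation among repeated measures of 0.5, and an alpha level of 0.05, 129 participants".
- **Dropout.** A 20% allowance raises 129 to 162, or 54 per group.
- **Background figures.** The section cites a minimal clinically significant difference of 4.25 FMA-UE points, and a mean difference of 4.50 points with SD 6 from an earlier robotic-therapy study.

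The Statistical analysis section plans a repeated-measures ANOVA to "examine the main effects of the group and time factors, as well as the group-time interaction effects". Simple-effect comparisons follow if the interaction is significant, and a Bonferroni correction is applied. No sphericity correction and no effect-size convention is stated in either section.

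**The concern.** G*Power is deterministic, so a full list of inputs should return the stated number. Here the inputs and the number disagree by a wide margin, and the direction of the disagreement depends on an effect that the text leaves open.

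The consequence is for interpretation. If the group main effect carries the conclusion, a null result would be read as coming from a trial with 80% power when, at the stated effect size, the power is close to one half. If the interaction carries it, the trial has far more power than claimed at that effect size, and the section misdescribes what was sized. A reader cannot tell which of these applies.

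**Working it through.** **Inputs** (Sample size calculation section): k = 3 groups, m = 5 measurements, correlation ρ = 0.5, α = 0.05, power 0.80, effect size 0.158. Two assumptions: 0.158 is Cohen's f, and ε = 1 because no correction is mentioned. Then f² = 0.158² = 0.024964. N is rounded up to a multiple of 3 for equal groups.

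**Formulas** (noncentral F, G*Power default convention):

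- Group main effect: λ = N f² m / (1 + (m − 1)ρ), df = k − 1 and N − k.
- Interaction: λ = N f² m ε / (1 − ρ), df = (k − 1)(m − 1)ε and (N − k)(m − 1)ε.
- Time: same λ as the interaction, df = (m − 1)ε and (N − k)(m − 1)ε.

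**Attempt to reproduce 129.** With N = 129 and ε = 1:

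- Group: λ = 129 × 0.024964 × 5 / 3 = 5.37, df 2 and 126, power 52.4%.
- Interaction: λ = 129 × 0.024964 × 5 / 0.5 = 32.2, df 8 and 504, power 99.3%.
- Time: λ = 32.2, df 4 and 504, power 99.8%.

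**N needed for 80% power:**

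| Effect | N required | Power at 129 |
|---|---|---|
| Group main effect | 237 (λ = 9.86) | 52.4% |
| Group-by-time interaction | 63 (λ = 15.7) | 99.3% |
| Time main effect | 51 (λ = 12.7) | 99.8% |

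129 is not reproduced for any of the three. With all 162 retained, the group main effect has λ = 6.74 and power 62.9%.

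**Other effect-size conventions.** In these, ρ plays no part.

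- Cohen, λ = N(m − 1)f²: interaction 153, time 123.
- SPSS, λ = (N − k)(m − 1)f²: interaction 156, time 126.

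The time figures come near 129, but the time effect is pooled over the arms.

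**Settings that do return 129** (default convention, unstated ε):

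- Time with ε = 0.25, the lower bound for five measurements (1/(m − 1)): λ = 8.05, df 1 and 126, power 80.4% at 129 and 79.5% at 126.
- Interaction with ε = 0.34: λ = 10.9, power 80.6% at 129 and 79.5% at 126.

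At ε = 0.25 the interaction has 70.9% power at 129.

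**Sensitivity of the group main effect.**

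- Power at 129 is 67% for ρ = 0.3, 52% for ρ = 0.5 and 39% for ρ = 0.8.
- 80% power at 129 needs f = 0.214; at 162 it needs f = 0.191.
- The cited 4.50 points and SD 6 give d = 0.75. With three means spanning that range and the third midway, f = 0.75 × √(1/6) = 0.306, and power at 129 is 98%.

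**Pairwise comparison at one visit.** Two-sample t-test, 43 per arm (129/3), d = 4.25/6 = 0.708, two-sided α = 0.05/3 = 0.0167: noncentrality 0.708 × √(43/2) = 3.28, power 79.8%.

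**Dropout step.** 129/0.8 = 161.25, raised to 162. This is correct.

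**The case against.** A reader might infer that the design lacks 80% power however its inputs are read, or that the trial is underpowered. The documents do not support either inference, for three reasons.

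1. With the default convention and ε = 1, 129 completers give 99% power for the interaction and 99.8% for time. What fails is the link between the inputs and 129, not 80% power under every test.
2. The 52% requires that the aim "the minimum sample size required to detect a significant between-group difference" means the group main effect averaged over all five visits, baseline included. The same words can simply mean that the arms differ, which the interaction also tests. The Statistical analysis section makes the interaction the condition for the simple-effect comparisons. On that reading there is no shortfall at f = 0.158 and ε = 1; at the lower-bound ε the power is 71%.
3. The 52% also requires f = 0.158. The difference and SD cited in the same section imply a larger f, with about 98% power for the group main effect at f = 0.306. In points, 43 per arm is roughly adequate for 4.25 at a Bonferroni-adjusted level.

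All three stand, and they limit the claim about power. They do not rescue the sentence, which presents 129 as the result of 0.158 and the other listed inputs. The routes that do return 129 use an undeclared ε, and the one at the lower bound is not a comparison of groups. Nor is this a matter of detail left out of a condensed article: the article prints an input list and a result, and the two disagree.

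**Conclusion.** The stated inputs do not yield 129 for any effect of the planned ANOVA. The required totals are 237 (group), 63 (interaction) and 51 (time), assuming that 0.158 is Cohen's f and that no sphericity correction applies.

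The practical meaning depends on the effect intended. For the group main effect at f = 0.158, the stated 80% is really 52% at 129 completers and 63% at 162. For the interaction at ε = 1, 129 is about twice the number needed (129/63 = 2.05). The document does not settle which was meant, so the firm conclusion is that the sample-size statement is wrong as written and its target is unnamed. Whether the trial is short of patients is not established.

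**What to change.** Keep 162 and rewrite the calculation paragraph:

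- Name the effect that the calculation is for.
- State any ε and effect-size convention that was used.
- Replace the 129/80% statement with the power that test really has. For the group main effect this is 52% at 129 (63% at 162) for f = 0.158, or 80% at 129 for f = 0.214. For the interaction it is 99% at 129 with ε = 1 and 71% with ε = 0.25.
- Alternatively, state the power of the pairwise comparison: 43 completers per arm give about 80% for 4.25 FMA-UE points at one visit, with SD 6 and two-sided α 0.0167.

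The cost is one corrected paragraph, with no change in recruitment. On the main-effect reading the stated power becomes less favourable.
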